#### Secondary outcomes

2.7.2

Brunstrom Recovery Stages for Upper Extremity will be used to assess severity of the deficits post stroke, it has good reliability and validity (35). Manual Muscle Test will be conducted on the key upper extremity and hand muscles. Passive and active range of motion will be measured of the key upper extremity and hand joints. The Modified Barthel Index is a 10-item scale with good reliability and validity, it is used to assess the patient’s ability to perform ADLs (36). The Functional Independence Measure will be used to measure the ability to carry out everyday tasks safely and independently, thus to determine burden of care, it’s reliability and validity are excellent (37).

#### fNIRS study

2.7.3

To study brain activation patterns and functional connection changes before and after the interventions, and to compare their difference between the two groups, each enrolled participant will be screened for fNIRS signal quality. Those with good signal quality will be evaluated using fNIRS. The NIRSport2 fNIRS device with 8 sources and 8 detectors, and its supporting data acquisition software Aurora fNIRS version 2021.9.0.6 (NIRx Medical Technologies, MN), will be used. The sampling rate will be set at 10 Hz. The regions of interest are the following Brodmann Areas (BA): BA6, BA7, BA40, BA44, and BA45, mainly the MNS; the montage design and its sensitivity have been confirmed in our previous study (21).

During the screen phase, the signal quality will be evaluated by the Aurora software’s default quality assessment function, it uses signal levels, dark noise and source brightness to reflect the signal quality, the signal level index is selected as the most important signal quality evaluation criterion. Signal level is the raw voltage reading at the detector, it reflects how well light passes through tissue, from a certain source to the detector. If this average value is high enough, the signal level of the channel formed by this source and detector will be marked as excellent (green, > 3 mV) or acceptable (yellow, > 0.5 mV and < 3 mV); if it is too low, it will be marked as critical (red, < 0.5 mV). If 80% of the channels’ signal levels are marked as green, the participant will be chosen to take part in the formal fNIRS assessments.

This fNIRS test protocol is designed to reveal the neural activity changes of a single session and multiple sessions (20 sessions over 4 weeks) of intervention (Figure 3). The test includes two sessions, one before the interventions (0 weeks) and one after the interventions (4 weeks). Three fNIRS testing runs will be conducted in each session: first, ~5 min resting state data will be collected; second, ~10 min task-related data will be collected; third, another ~5 min resting state test will be conducted after finishing the tasks. In each fNIRS test session, participants will seat in a comfortable and relaxed upright position. In the resting state test, participants will be asked to keep still and silent, trying their best to relax as much as possible without thinking about anything, but not falling sleep. The task experimental program adapts a block design with two different conditions: VRAO+NMES and VRLO+NMES. Each block will last 35 s, including 20 s of rest and 15 s of task. Each experimental task will be cycled 8 times. The fNIRS data pre-processing and analysis will be conducted in MatLab R2017b (MathWorks, MA), including individual analysis and group-level analysis (21).

**Figure 3 fig3:**
[figure not shown]
Schematic illustration of the fNIRS experimental paradigm. fNIRS, functional near-infrared spectroscopy; VR, virtual reality.

##### Resting-state fNIRS data preprocessing and analysis

2.7.3.1

The resting-state fNIRS data will be pre-processed by the FC-NIRS Matlab package (38). Firstly, the signal quality will be assessed by the signal-to-noise ratio, between-channel signal correlation, and frequency spectrum analysis. Secondly, the channels with poor quality will be considered as bad channels and removed from analysis. The participants with 5 or more bad channels will be excluded from the analysis. Thirdly, the spline interpolation method will be used to eliminate motion artifacts. Fourthly, the Principal Component Analysis (PCA) algorithm will be used to perform global signal regression to reduce the effect of global noise (arterial pulse, respiration, and cardiac pulsation etc.). Fifthly, the influence of low-frequency drift and high-frequency physiological noise will be reduced by the bandpass filter method with a range of 0.01–0.1 Hz. Sixthly, the hemoglobin (Hb) concentration changes will be calculated according to the modified Beer–Lambert law (mBLL), including oxygenated hemoglobin (HbO) and deoxygenated hemoglobin (HbR). Seventhly, stable Hb time series will be extracted for each participant (39). Finally, the topological properties of the brain network will be calculated based on graph theory, including the global network metrics (clustering coefficient, characteristic path length, global and local efficiency etc.) and nodal network metrics (nodal degree, nodal efficiency, and nodal betweenness) (38).

##### Task fNIRS data preprocessing and analysis

2.7.3.2

The task related fNIRS data will be analyzed by the NIRS Brain AnalyzIR Toolbox (40). Firstly, the task related fNIRS raw data (light intensity) will be converted into optical density. Secondly, Hb concentration changes will be calculated according to the mBLL (41). Thirdly, the autoregressive iteratively reweighted least squares (AR-IWLS) general linear model (GLM) algorithms will be used to quantitatively analyze the relationship between brain signal and stimulus, the regression coefficient (*β*) will be calculated. Fourthly, the linear mixed-effect model will be used in the group-level analysis, the estimated value of β and its corresponding standard error will be calculated, treating participants as random effects. The false discovery rate (FDR) method will be used to obtain multiple comparison correction *p*-values (P_FDR_) (42). Fifthly, after channel level data analysis, based on the probability registration method, the activation results of each region-of-interest will be obtained. Finally, the brain activation results will be visualized on the Colin27 standard brain (21).

#### sEMG study

2.7.4

The UMI-SE-I sEMG recording and analysis system (United Medical Equipment Co., Ltd., Shaoxing, China) will be used in the sEMG sub-study. The main parameters of this device are: sampling rate of >3 kHz, resolution of 0.1 μV, passband width of 15–1,000 Hz, common mode rejection ratio of >110 db, and noise of <1 μV. Disposable Ag/AgCl electrodes will be used to collect data after the skin is wiped by 75% medical alcohol. The electrodes will be adhered along the extensor digitorum and extensor carpi radialis muscle fibers according to the guidance of the instrument’s guiding program. The average electromyography value will be calculated and used for analysis. Three trials with high signal quality will be selected for each test action.

### Patient withdrawal, risks, and benefits

2.8

Any participant can withdraw consent at any time during the study, without any consequences. The study will be terminated under the following conditions: new serious disease leading to unstable vital signs, medical complications, hospital discharge, new emotional or psychological problems, and inability to cooperate with the assessment; patients or their families refuse to continue the study. All the potential benefits and risks of the study will be discussed with participants and their caregivers during the initial visits (29).

### Adherence reminder sessions

2.9

To promote participation and adherence to the protocol, a video of the study introduction will be shown to the potential participants and their caregivers. A study brochure will be given to all the enrolled participants and their caregivers, including brief introduction of the study, calendar reminder of all the important study events, and treatment self-record tables. The participants will also get a information card with the telephone and email contact information of the PI printed on it. For those who do not complete the full study, their data will be used for a further sub-analysis.

### Sample size

2.10

The primary outcome of this study is FMA-UE. A power analysis of the independent sample t-test was conducted using R package pwr version 1.3.0. According to a previous study, the effect size (d) was set at 0.8, the significance level was 0.05, and the power was 0.85; the calculated sample size was 60 participants in total, 30 participants in each group (43). Based on a dropout rate of 5%, it is estimated that 32 participants need to be recruited in each group.

### Data management and confidentiality

2.11

Specific tables and forms were designed to collect the research data, including case report forms (CRFs), adverse events (AEs), serious adverse events (SAEs), treatment records, clinical scales and questionnaires. The data will be recorded firstly in paper data collection forms, and then be entered into an electronic database. To maintain data quality and integrity, double entry, valid value, range check, and random recheck and review will be conducted. The study files will be kept by the research group for at least 5 years after the completion of the trial. Only the PI and authorized personnel will have access to the study data. However, the study records may be reviewed by the Medical Ethics Committee of CRRC and relevant scientific research management and regulation institutions. All the group members will be trained to master the SOPs of the intervention and evaluation methods, thus to improve standardization of the study and improve data quality.

The printed paper forms, records, and other materials will be locked in a drawer in the research office. The electrical data will be stored in a password-protected database installed on a laptop. As the data custodian, the PI will hold the key to the drawer, keep the password of the database and laptop. To protect the participants’ privacy, the research team will maintain confidentiality of the paper and electrical trial files. Each participant will be assigned a unique identification (ID) as a secret code; minimum personal data will be collected and kept. The coded participant level data will be described anonymously and will not be shared. All the information that could identify a specific participant will be recorded only on the informed consent forms, including name, resident ID, contact details, and address. The research management departments will monitor and audit the records without violating confidentiality.

### Statistical analysis

2.12

For continuous variables, Shapiro–Wilk normality tests will be performed to assess their normality. Data following normal distribution will be expressed as mean ± standard deviation (SD), while the non-normal distributed data will be described as median and interquartile range (IQR). If each group’s data conforms to normal distribution and homogeneity of variance, the independent sample *t*-test will be used to compare the inter-group difference, and the paired *t*-test will be used to compare the intra-group difference pre- and post-interventions. If the data does not conform to normal distribution and homogeneity of variance, the non-parametric tests will be used for comparisons between and within groups. The categorical variables will be expressed as frequency and percentage; Chi-square test will be used for comparison between and within groups. Pearson or spearman correlation analysis will be used to test the correlation between variables according to their distributions. The significance level will be set as *α* = 0.05. We will use R version 4.2.3 and RStudio version 2024.04.21 (Posit Software, MA) to conduct the statistical analysis (44).

All the analyses will be conducted based on the Intention-To-Treat principle. For participants who quit the study midway, a subgroup analysis will be conducted with the collected outcome data. After the first 20 participants have finished all the evaluations, an interim analysis will be conducted according to the statistical analysis plan.

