#### Exclusion criteria

2.4.2

Participants will be excluded if they meet one of the following criteria: (1) With serious diseases, such as heart, lung, liver, and kidney failure; (2) With other neurological conditions that cause motor deficits, such as Parkinson’s disease, multiple sclerosis, and peripheral neuropathy; (3) Epileptic seizures; (4) With cognitive impairments, Mini-Mental State Examination (MMSE) ≤24 scores, unable to cooperate with researchers to finish the interventions or assessments; (5) With severe aphasia and communication difficulties that may influence the intervention and outcome measures; (6) With severe pain, Visual Analog Scale (VAS) ≥7 scores; (7) With moderate or severe depression, anxiety and other psychological disorders; (8) With contagious conditions or diseases, particularly of eyes, skin, scalp, or forearm; (9) With implanted medical devices or materials, such as pacemaker and metal implants; (10) With contraindications for NMES, such as skin injuries or skin diseases, acute infections, vascular diseases in the affected forearm; (11) With other diseases limiting upper extremity and hand functions, such as fracture, joint injury, and muscle pain of the affected arm; (12) With vestibular diseases, digestive problems that limit the use of VR headset; (13) Surgery and other invasive treatments; (14) Participants with a recurrent stroke or any medical condition that may affect safety or accuracy of evaluation results will also be excluded (29).

In addition, we will use structural MRI to calculate lesion volumes, including hemorrhage size (for hemorrhagic strokes) and infarct volume (for ischemic strokes). Automated or semi-automated segmentation tools (e.g., MRIcron, ITK-SNAP) will be applied to ensure accuracy and reproducibility (30). Lesion locations will be mapped to standardized brain atlases [e.g., Montreal Neurological Institute (MNI) space] using voxel-based or region-of-interest approaches. This will allow precise documentation of cortical/subcortical involvement (e.g., motor cortex, corticospinal tract, parietal regions) (31). Participants will be stratified into subgroups based on stroke type, lesion volume and location. What’s more, we will meticulously record the time elapsed from stroke onset to the initiation of rehabilitation, including the start of conventional rehabilitation therapy and AOT.

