### Randomization and blinding

2.5

Through a computerized block randomization protocol, the participants meeting the eligibility criteria will be randomly assigned to control group or experiment group. The random allocation sequence will be generated by the R package blockrand version 1.5, with randomly ordered blocks of size 6 or 8, and a 1:1 allocation ratio. The randomization cards generated by the blockrand version 1.5 package will be printed out and enclosed in sequentially numbered, opaque, sealed, and stapled envelopes. The allocation sequence will be concealed from the researcher responsible for enrolling and evaluating participants. Corresponding envelopes will be opened only after the enrolled participants have completed all the baseline assessments and at the time of allocation to the intervention. An independent study coordinator who will not oversee assessments and interventions will design and conduct the randomization sequence generation and group allocation. Only the study coordinator and principal investigator (PI) have access to group assignment materials locked in a binder.

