### Outcomes

2.7

All participants will be evaluated by clinical scales, fNIRS, and sEMG before and after 4 weeks of interventions. At baseline, sociodemographic and neurologic data will be collected, including age, gender, Body Mass Index, education, medical history, type of stroke, location of injury, and duration of disease. In addition, questionnaire surveys about safety, satisfaction, and feedback will be performed at the end of the interventions. Adverse events and serious adverse events will be monitored from the beginning to the end of the study. Expert therapists with above 10 years of experience will conduct the functional measures.

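### The FMA-UE comparison between arms has no baseline adjustment and its test is chosen by pretests; prespecified ANCOVA would be more precise without new data

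*Protocol article*

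**What the plan says.** Section 2.10 states: "The primary outcome of this study is FMA-UE". It sizes the trial on an independent sample t-test with d = 0.8, significance level 0.05 and power 0.85, giving 30 per group, or 32 after 5% dropout.

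Section 2.12 sets one rule for all continuous variables. Shapiro–Wilk "normality tests will be performed to assess their normality". If each group passes for normality and equal variance, the independent t-test "will be used to compare the inter-group difference", with paired t-tests within each arm. If the data "does not conform to normal distribution and homogeneity of variance, the non-parametric tests will be used", both between and within groups. No covariate is named for any clinical outcome. The only group-level regression model in the article is the mixed model for task fNIRS (section 2.7.3.2). Section 2.12 refers to a statistical analysis plan only for the interim analysis.

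On the baseline, section 2.7 says: "All participants will be evaluated by clinical scales, fNIRS, and sEMG before and after 4 weeks of interventions". Section 2.5 says: "Corresponding envelopes will be opened only after the enrolled participants have completed all the baseline assessments". Allocation is generated "with randomly ordered blocks of size 6 or 8, and a 1:1 allocation ratio", and no stratification factor is named.

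**The concern.** Entry covers Brunnstrom stages 3 to 5 and any time up to 6 months after stroke (section 2.4.1). Starting FMA-UE will therefore vary between patients, and it can be expected to predict the week-4 score. It is measured before the envelope is opened, so it is a proper covariate. Nothing in the allocation balances it.

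Two things are at stake. The first is precision. A t-test on week-4 scores ignores the baseline. A t-test on changes uses it, but with its coefficient fixed at 1 instead of estimated. ANCOVA does at least as well as both, apart from the small cost of estimating one slope. The second is the estimand. The t-test gives a difference in FMA-UE points; a rank test does not. Under the stated rule, the observed data decide which of the two the trial reports.

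**Working it through.** **Inputs.** From section 2.10: d = 0.8, alpha = 0.05 (two-sided assumed, since sidedness is not stated), power 0.85, 30 per group, 5% dropout. Not in the document: the correlation r between baseline and week-4 FMA-UE (assumed 0.5 to 0.8), and whether d refers to the SD of week-4 scores or of changes. Both readings are worked below.

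**1. The plan's own figure.** The two-sided t-test (noncentral t) needs n = 29.05 per group, rounded up to 30. Then 30/0.95 = 31.6, rounded up to 32. Both stated numbers reproduce. Power at 30 per group is 0.861.

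**2. Variance of the estimate, with equal SD at both visits.** Let σ be that SD.
- t-test on week-4 scores: outcome variance σ².
- t-test on changes: 2σ²(1 − r).
- ANCOVA: residual variance σ²(1 − r²).

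So ANCOVA has 1 − r² times the variance of the week-4 t-test. Against the change-score t-test the ratio is (1 − r²)/[2(1 − r)] = (1 + r)/2.

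**3. Power at 30 per arm.** The effective d is 0.8 divided by the square root of the variance ratio, with 57 degrees of freedom. The planned t-test has power 0.861 in every row.

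| d = 0.8 refers to | r | Variance ratio | SE ratio | Effective d | ANCOVA power |
|---|---|---|---|---|---|
| week-4 SD | 0.5 | 0.75 | 0.866 | 0.924 | 0.940 |
| week-4 SD | 0.7 | 0.51 | 0.714 | 1.12 | 0.989 |
| week-4 SD | 0.8 | 0.36 | 0.600 | 1.33 | 0.999 |
| change SD | 0.5 | 0.75 | 0.866 | 0.924 | 0.940 |
| change SD | 0.7 | 0.85 | 0.922 | 0.868 | 0.910 |
| change SD | 0.8 | 0.90 | 0.949 | 0.843 | 0.894 |

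The gain grows with r under the first reading and shrinks with r under the second. The table leaves out the cost of estimating the slope. With 60 patients that cost is about 1 + 1/56 = 57/56 in variance, or 0.9% in SE, which is smaller than every gain shown.

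**4. The pretest gate.** 6,000 simulated trials per scenario, 30 per arm, with Shapiro–Wilk in each arm and a Levene test at 5%. Failure of any one led to Mann–Whitney. The document names neither the variance test nor the rank test, so both are assumptions.
- Normal data, no effect: 14% of trials are sent to the rank test; type I error of the whole rule 0.051.
- Skewed, bounded data (an assumed Beta(2,1) shape scaled to 0–66), no effect: 76% are sent to the rank test; type I error 0.043.

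The gate therefore often changes what is estimated, and in these scenarios it did not inflate the error rate.

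**The case against.** The strongest reply is that nothing here is invalid. An unadjusted comparison in a randomised trial is unbiased, and its standard error already allows for chance baseline imbalance. The sample size was calculated for the very test that is planned, and it reproduces. All of that stands, so this is a point about efficiency and prespecification.

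A reader might infer more than the document supports:

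- **That the plan throws the baseline away.** This is true only if week-4 scores are compared. Section 2.12 does not say, and section 2.7.1 frames the hypothesis as patients reaching a 4.25-point difference, which suggests change from baseline. If changes are compared, the gain is smaller. For example, with d = 0.8 on the week-4 SD and r = 0.7, a change-score t-test already has power 0.976 against 0.989 for ANCOVA.
- **That the gate inflates type I error.** The simulated error stayed near 5%. Clear inflation would need strongly unequal variances, for which the article gives no basis.
- **That subgroup analyses will split the trial into tiny cells.** Section 2.4.2 says "Participants will be stratified into subgroups based on stroke type, lesion volume and location", but gives no number of categories, no cross-classification and no test within strata.
- **That within-arm tests will carry the efficacy claim.** The between-arm test is the powered one, and section 2.1 describes a randomised comparison. The paired tests call only for a rule on how they are reported.

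**Conclusion.** The point holds as a worthwhile improvement that needs no extra data. It does not show bias or a wrong sample size. The method is stated in the article, so this is not a detail left to an unseen analysis plan. Within the assumed r of 0.5 to 0.8, ANCOVA lowers the standard error by 13% to 40% against a t-test on week-4 scores, and by 13% to 5% against a t-test on change scores. The direction is the same under both readings. The size depends on r and on which score d refers to, and the document gives neither. The data-driven choice between a mean difference and a rank comparison is a separate weakness that does not depend on r.

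**What to change.** In section 2.12 and the statistical analysis plan:

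1. Name one primary analysis: ANCOVA of week-4 FMA-UE on arm and baseline FMA-UE, reporting the adjusted mean difference in points with its 95% confidence interval. This also settles the choice between week-4 and change scores.
2. Remove the normality and variance gate for this outcome. Keep robust standard errors, or a rank-based or permutation analysis, as sensitivity analyses only.
3. State that efficacy conclusions rest on the between-arm estimate and that within-arm changes are descriptive.
4. Further covariates such as Brunnstrom stage are optional. If used, name them in advance.

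The cost is a wording change. Baseline FMA-UE is already collected, and no extra patients or visits are needed. The planned 32 per group can stay.

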#### Inclusion criteria

2.4.1

Participants will be included if they meet the following criteria: (1) Patients with a first-ever ischemic or hemorrhagic stroke, meeting the stroke diagnostic criteria established by the fourth National Conference on Cerebrovascular Disease of China in 1995, and confirmed by computerized tomography (CT) or magnetic resonance imaging (MRI); (2) Adults, aged 30–70 years old; (3) Within 6 months of stroke onset; (4) The disease is stable, neurological conditions and vital signs are no longer progressing; (5) The ability to sit independently for approximately 40 min to finish the treatments and assessments, including preparing time; (6) Without visual impairment, able to see the content of the experiment program; (7) Unilateral limb hemiplegia, Brunstrom Recovery Stages for Upper Extremity 3, 4, or 5 stage at the time of enrollment; (8) Right-handed, determined by the Edinburgh Handedness Inventory (EHI) – Short Form (28); (9) Chinese speaking; (10) Junior high school education or above; and (11) Willingness to provide informed consent and comply with the study protocol.

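### The within-group (pre versus post) comparison of categorical variables is assigned the chi-square test, which assumes independent observations although the data are paired

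*Protocol article*

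**What the plan says.** Section 2.12 (Statistical analysis) gives one rule for all categorical variables: "Chi-square test will be used for comparison between and within groups".

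For continuous variables the same paragraph treats the two comparisons differently. Groups are compared with the independent-sample t-test, while "the paired *t*-test will be used to compare the intra-group difference pre- and post-interventions". Within-group therefore means before versus after treatment. Section 2.7 (Outcomes) confirms that the measurements are repeated on the same people: "All participants will be evaluated by clinical scales, fNIRS, and sEMG before and after 4 weeks of interventions".

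Two secondary outcomes in section 2.7.2 are recorded as stages or grades: "Brunstrom Recovery Stages for Upper Extremity will be used to assess severity of the deficits post stroke", and "Manual Muscle Test will be conducted on the key upper extremity and hand muscles". For the first, section 2.4.1 limits entry to a few levels ("Brunstrom Recovery Stages for Upper Extremity 3, 4, or 5 stage at the time of enrollment"). The article does not say whether either is analysed as categorical or as a score.

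On the error rate, section 2.12 says "The significance level will be set as *α* = 0.05", without stating sidedness.

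**The concern.** The Pearson chi-square test compares two independent samples. Applied to before and after frequencies, it counts each patient twice, as if 30 patients per arm were 60 unrelated people, and it ignores how many individuals actually changed category. Information about change lies in the patients who move, and the test does not use it.

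If before and after values are positively correlated, the standard error is too large. Real improvement within an arm can then be missed, and the reported p-value does not have its stated meaning. The article respects pairing for continuous data and drops it for categorical data two sentences later. Because it names a specific test, this is not a detail left open for the analysis plan.

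**Working it through.** **1. Number of pairs.** Section 2.10 states that "the effect size (d) was set at 0.8, the significance level was 0.05, and the power was 0.85", giving 30 per arm. Normal approximation: n = 2(1.960 + 1.036)²/0.8² = 28.1, so 29. The two-sided two-sample t-test gives 29.05, rounded up to 30. With 5% dropout, 30/0.95 = 31.6, so 32. The article's figures reproduce. I use 30 pairs per within-group test and a two-sided 0.05.

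**2. Why the size is wrong.** Let p be the proportion in a category, unchanged over time, and φ the within-person correlation of the binary variable.

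- True variance of the before-after difference: 2p(1 − p)(1 − φ)/n.
- Variance used by the chi-square test: 2p(1 − p)/n.
- Approximate actual size: 2[1 − Φ(1.96/√(1 − φ))].

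At φ = 0.5, 1.96/√0.5 = 2.77, which gives 0.0056. At φ = 0.3 and 0.6 the formula gives 0.019 and 0.0019.

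**3. Exact size.** The article gives no φ, so I assume a range. I enumerated all tables of 30 pairs with p = 0.5 and no true change:

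| φ | Chi-square ignoring pairing | McNemar, asymptotic | McNemar, exact |
|---|---|---|---|
| 0 | 0.052 | 0.048 | 0.028 |
| 0.3 | 0.020 | 0.043 | 0.023 |
| 0.5 | 0.006 | 0.045 | 0.018 |
| 0.6 | 0.0025 | 0.048 | 0.013 |

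At φ = −0.3 the chi-square size is 0.089, so the direction depends on the sign of the correlation.

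**4. Power for a true rise from 40% to 60%, 30 pairs.** The both-times cell is 0.4 × 0.6 + 0.24φ. At φ = 0.5 it is 0.36, so 0.40 − 0.36 = 0.04 worsen and 0.60 − 0.36 = 0.24 improve.

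| φ | Chi-square | McNemar, asymptotic | McNemar, exact |
|---|---|---|---|
| 0.3 | 0.32 | 0.42 | 0.33 |
| 0.5 | 0.29 | 0.57 | 0.43 |
| 0.6 | 0.26 | 0.72 | 0.51 |

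**5. One example.** Suppose 10 of 30 patients are in a category before and 18 of 30 after, with 8 moving up and none down. The chi-square statistic is 4.29, p = 0.038 (0.070 with Yates correction). Exact McNemar gives 2 × 0.5⁸ = 0.008.

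**6. Three categories.** In 20,000 simulated trials with 30 pairs, three equally likely categories and no change, the chi-square size is 0.022, 0.012, 0.006 and 0.002 at latent correlations of 0.5, 0.7, 0.8 and 0.9.

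**7. The other possible layout.** If the chi-square test were run on the before-by-after cross-table, it would test association, not change. With φ = 0.5, p = 0.5 and no true change it rejects about 80% of the time. Neither layout answers the within-group question.

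**The case against.** **McNemar may have been meant.** Its statistic is referred to a chi-square distribution, and an article condenses. But the same phrase covers the comparison of independent groups, where McNemar cannot apply, and no paired categorical test is named anywhere. The wording still needs correcting.

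**It may affect few variables.** This largely stands. The plainly categorical variables in section 2.7 (gender, stroke type, lesion location) are collected at baseline only. Brunnstrom stage and Manual Muscle Test grade could go through the non-parametric route that section 2.12 provides for non-normal continuous data, since their data type is not stated. For the same reason, a reader might infer that the between-group chi-square wastes the ordering of these scales; the article does not say they will be analysed that way.

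**The hypotheses are between groups.** This also stands. Superiority is claimed over the control arm, and within-arm change cannot establish it. A reader might think the responder result is affected. It is not: reaching 4.25 points on the FMA-UE (section 2.7.1) is one value per patient, derived from change and compared between arms, with no baseline counterpart.

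**The loss may be small.** At φ = 0.3, exact McNemar gains almost nothing in power (0.33 against 0.32), and it is itself conservative, with size 0.013 at φ = 0.6. A reader might conclude that the planned p-values are certainly far too conservative; that needs at least moderate positive correlation, which is plausible for motor stage over four weeks but assumed here.

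**Conclusion.** The rule is wrong as written: a test for independent samples is fixed for paired observations, and its within-group p-values are not valid at any non-zero pre-post correlation. With positive correlation and the before-versus-after layout, the actual size falls from 0.05 to between about 0.020 (φ = 0.3) and 0.0025 (φ = 0.6). The power lost relative to asymptotic McNemar runs from 0.42 − 0.32 = 0.10 to 0.72 − 0.26 = 0.46. These sizes rest on an assumed φ, 30 complete pairs, a two-sided test and no continuity correction.

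The reach is limited to secondary within-group results on variables that are categorical, or are treated as such. The primary FMA-UE analysis, the responder comparison between arms and the sample size are unaffected, and between-group chi-square tests are not invalidated. Severity is minor to moderate.

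**What to change.** Replace the sentence in section 2.12 with separate rules for the two comparisons:

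- **Within groups, binary:** McNemar, asymptotic or mid-p. If the exact version is chosen, note its conservatism.
- **Within groups, ordered categories:** Wilcoxon signed-rank or a marginal homogeneity test. This covers Brunnstrom stage and Manual Muscle Test grade if they are treated as categorical, and the text should say whether they are.
- **Between groups, unordered categories:** keep chi-square, with Fisher's exact test for small counts.

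The cost is a sentence or two in the analysis plan. The tests are standard, no further data are needed and the sample size does not change. The change should be made before outcome data are analysed, including the interim analysis planned after the first 20 participants.
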